## Abstract

**Background:**

Strokes are a common cause of adult disability and mortality worldwide. Transient ischaemic attacks (TIA) are associated with a high risk of subsequent stroke, and rapid intervention has the potential to reduce stroke burden. This study will assess a novel electronic decision support (EDS) tool to allow general practitioners (GPs) to implement evidence-based care rapidly without full reliance on specialists.

**Methods/design:**

This is a cluster randomized controlled trial comparing TIA/stroke management of GPs with access to the EDS tool versus usual care. The intervention period is 12 months with a 3-month follow-up period for individual patients. Primary outcomes consist of stroke within 90 days of presenting event and adherence to the New Zealand national TIA guideline.

**Discussion:**

A positive study will provide strong evidence for widespread implementation of this tool in practice and has the potential to improve key outcomes for patients and reduce the burden of stroke.

**Trial registration:**

Australia New Zealand Clinical Trials Registry ACTRN12611000792921

## Background

Stroke is the second most common cause of death worldwide and the most common cause of long term adult disability in developed countries [1,2] Stroke costs New Zealand over $450 million every year [3]. If current trends in stroke incidence and mortality continue [4-6], the number of stroke survivors in New Zealand will reach 50,000 by 2015 [7], with overall annual costs of > $700 million. Reducing the burden of stroke is a key goal for health service planning [8].

Transient ischaemic attacks (TIAs) identify people at high risk of stroke. TIA is defined as transient loss of focal cerebral or ocular function lasting <24 hours, attributable to ischaemic vascular disease. TIAs precede stroke in approximately 25% of stroke victims. The 24-hour cutoff point is arbitrary and minor strokes, defined as symptom duration of >24 hours but with subsequent complete or near complete recovery, carry the same high risk of subsequent stroke as TIAs. Both indicate circulatory compromise of brain tissue that is at risk of infarction, but which is yet entirely or nearly entirely salvageable.

Transient cerebral ischemia is typically caused by unstable plaques affecting the larger vessels that supply large amounts of brain tissue. As a result, the majority of strokes that follow TIA or minor stroke are severely disabling or fatal, and these are most likely to occur within 48 hours and up to seven days following TIA while the plaque remains ‘fresh’ [9]. This highlights the importance of urgent intervention to maximize stroke prevention in high-risk patients. A key intervention that reduces subsequent stroke is rapid initiation of best medical therapy via urgent (<24 hour) specialist review [10,11]. Care following this model has been associated with an 80% reduction in 90-day stroke risk from 10.3% to 2.1% (adjusted hazard ratio 0.20, 95% CI 0.08 to 0.49; p = 0.0001) [10].

In New Zealand, providing 24-hour, seven days a week, rapid access specialist TIA clinics is challenging, especially in the smaller district health boards (DHBs), where patient numbers cannot support a sufficient number of neurologists/stroke physicians to staff an around-the-clock specialist service. A UK study has shown that most patients experiencing TIA or minor stroke first seek healthcare from their general practitioner (GP) [12], even when the event occurs outside normal working hours. Thus, in a setting of limited specialist access it seems logical to look for ways that urgent intervention could be offered at the GP level in order to avoid unnecessary and potentially life-threatening treatment delays. However, the scope of clinical conditions managed in general practice is very broad, and individual GPs will have patients presenting to them with TIA/stroke relatively infrequently. Our analysis of general practice records suggests that, on average, a GP will be consulted four to five times per year by a patient presenting with a presumed TIA/minor stroke. However, GP diagnostic accuracy of TIA/minor stroke is only 50% to 80% [13], so the actual rate of recognized TIA/minor stroke patients encountered by GPs may be as few as two to three patients per year.

Electronic clinical decision support systems (EDS) may be especially valuable for assisting clinical decision-making in such circumstances, where a condition is both challenging to diagnose correctly and encountered by generally clinicians relatively infrequently. New Zealand’s MidCentral Stroke Service, in collaboration with the Best Practice Advocacy Centre Inc. (BPAC), has developed a novel TIA/stroke EDS tool. The tool may mitigate the problem of limited or delayed specialist assessment in a setting in which many GPs lack the experience necessary to manage TIA/stroke independently. It aids GPs to accurately diagnose TIAs, promoting treatment initiation at first point of contact rather than awaiting specialist review, and prompts GPs to manage TIA and stroke patients comprehensively and in accordance with New Zealand guidelines [13].

One of the benefits of the EDS tool is that it is inherently educational, providing GPs with immediate feedback on diagnosis and guideline based advice, which can be applied to the management of future patients and improve diagnostic and management skills over time.

Throughout New Zealand, similar BPAC decision support modules are used by 76% of general practices and 85% of GPs. The TIA/stroke module differs from other existing modules because it focuses on the management of an acute medical problem rather than chronic care or disease prevention. However, in its operation it mimics other existing tools. The TIA/stroke tool is a new module that has so far been used only in the MidCentral DHB. National implementation of the TIA/stroke decision support module has the potential to significantly reduce the burden of stroke throughout New Zealand. However, its use may also involve two main possible threats to patient safety: patients may be erroneously diagnosed as not having a TIA and miss out on early treatment and/or specialist referral; and patients may be erroneously diagnosed with a TIA and placed needlessly on potentially harmful medications such as aspirin.

There has been no research investigating impacts of any BPAC EDS modules on clinical behavior and patient outcomes in New Zealand. International evidence on whether point-of-care decision support improves patient care has been equivocal [14,15]. Decision support tools are becoming ubiquitous throughout New Zealand primary care and their utility should be carefully evaluated. In particular, do they assist clinicians to make evidence-based clinical decisions? In a literature review, we identified 175 published reports of research into EDS use in primary care settings, but no tool that addresses the complex clinical care needed for initial presentation of TIA/stroke. Systematic reviews of the decision support literature conclude that there is a shortage of well-designed randomized controlled trials of EDS that provide assessments of its effectiveness in changing patient outcomes, as well as in changing clinician behavior [16-21].

To date, we have conducted four studies to assess the TIA/stroke decision support tool. A pre-launch community-based pilot indicated a high degree of GP satisfaction, excellent guideline adherence when the tool’s management advice was followed closely, and no adverse patient outcomes [22]. A second study comparing stroke experts, GPs, and decision support management in seven sample cases found that management was guideline adherent 33% among GPs without EDS, 92% among specialists, and 100% when the decision support tool was used [23]. Data from a before-and-after study in the MidCentral DHB showed that best medical therapy was in place within 24 hours in 31% of patients before introduction of the EDS system and 52% after its introduction [24]. Finally, a recent unpublished audit of all patients managed using the EDS for the 18 months following its launch has not found any significant adverse events associated with its use. Although reassuring and promising these small non-experimental studies support the need for a well-designed randomized controlled trial to assess this novel treatment approach.

The aim of the FASTEST trial is to formally test the efficacy and safety of New Zealand’s TIA/stroke decision support tool in comparison with usual care. This study has received funding from the Health Research Council of New Zealand (grant 11/268), ethics approval from the Ministry of Health Multi-region Ethics Committee (URA/11/08/048) and has been under way since November 2011.

## Methods/Design

### Design

Cluster randomized controlled trial of general practices with and without TIA/stroke EDS, comparing TIA and stroke management strategies, outcomes, and cost in each arm.

### Intervention

The decision support tool is an internet-based module provided and maintained by BPAC. GPs access this tool by clicking a menu button situated on the navigation bar of their practice management software that links them to the BPAC module site. From there they select the TIA/stroke tool from a menu. Once selected, a single page of tick boxes opens up for GPs to complete covering items such as relevant aspects of presenting illness history and a brief focused physical examination. Fields for relevant past medical history (*e.g.*, diabetes and smoking history) are automatically populated by extracting data directly from the practice management system (Figure 1).

**Figure 1 F1:**
[figure not shown]
TIA/stroke EDS Data Entry Form with sample case.

Completing the page of background and clinical presentation data takes approximately two to five minutes depending on the GP’s familiarity with the tool. Based on this information, the software confirms or rejects TIA/stroke as the likely diagnosis. If TIA or stroke is confirmed, a triage recommendation is generated based on the validated ABCD2 risk score [25] supplemented by several other variables taken from the New Zealand TIA guidelines [13] (Figure 2). If patients are triaged into the ‘low risk’ category, GPs are offered the option of either referring them to a TIA clinic for specialist review within seven days or of managing the patients themselves in the community. If community management is selected, a step-by-step outline is provided with links to pre-populated relevant prescriptions, radiology referral forms, and a variety of patient information leaflets (Figure 3). If patients are triaged into the ‘high risk’ category, GPs are advised to refer them to hospital immediately for specialist assessment and diagnostic work-up to be achieved within 24 hours, and GPs are not offered the community management option. However, if a GP feels that urgent hospital referral is not appropriate in any given situation (*e.g.*, the patient refuses to attend the Emergency Department), then GPs have the option to override this recommendation and refer patients to an outpatient specialist TIA clinic instead, as long as a reason for overriding the recommendation is specified. Hospital referral forms are automatically generated and contain all information needed for specialists to prioritize patients appropriately. In the case of a hyper-acute stroke with unresolved symptoms that started within the preceding 4.5 hours (*i.e.*, within the thrombolysis window) the tool is immediately aborted and the GP is advised to call 111 for emergent hospital transfer to a centre where stroke thrombolysis is available.

**Figure 2 F2:**
[figure not shown]
Sample Outcome Page for a low-risk patient with typical TIA symptoms.

**Figure 3 F3:**
[figure not shown]
Sample ‘comprehensive TIA/stroke work-up in the community’ instructions for low-risk TIA patient with typical anterior circulation symptoms.

To preserve patient confidentiality, all patient data for the study generated by the decision support tool are transmitted in an encrypted format to BPAC and from there to the research team.

### Outcome measures

The two primary outcome measure are recurrent stroke within 90 days of initial presentation with TIA or stroke and management in accordance with New Zealand TIA guidelines with regard to: treatment with anti-platelet therapy being achieved within 24 hours of presentation; treatment with statin, anti-hypertensive, and/or warfarin (if applicable and not contraindicated) being achieved as soon as clinically indicated and deemed safe; and receipt of appropriate diagnostic investigations within 24 hours or seven days based on risk stratification.

Secondary outcomes include: adverse events (including, but not limited to, medication side effects, diagnostic delays, and misdiagnoses); occurrence of recurrent TIA, myocardial infarction, major bleeding, and/or death within 90 days; implementation of a comprehensive adjuvant treatment plan (smoking cessation counseling, exercise/diet advice, communication of driving restrictions, and education on thrombolysis); overall treatment cost (including both direct cost relating to treatment of index event and cost of any events related to presenting complaint during the follow-up period); and GP and TIA clinic specialist satisfaction.

### Sample size calculation

The primary outcome is the proportion of participants who have recurrent stroke within 90 days of the presenting TIA/stroke. Based on previous work [9,11,24], we estimate that 10% of patients in the control group will have a stroke or TIA compared to 2% of patients in the intervention group.

Unadjusted for the cluster design, a total sample size of 274, one-half in each of two treatment arms, is needed to detect this size difference with 80% power and type I error rate of 5% [26]. We planned to recruit 40 practices, representing clusters, and used an intra-class correlation coefficient of 0.01 similar to the median intra-class correlation in the paper of Adams [27]. Based on an average of seven participants per practice, the adjusted sample size needed is 292.

This is achievable in 12 months assuming an average of 2.5 GP full-time equivalents per practice and an average of two to three TIA/minor stroke patients per GP per year. The sample size calculation also takes into account an expected 50% to 80% [13] GP diagnostic accuracy. We anticipate that an average of four to five patients will be registered in the study per GP over 12 months, but with an average of only two to three patients having actually suffered a true TIA or minor stroke.

A pre-specified second primary outcome is the proportion of patients who receive management according to New Zealand TIA guidelines. This outcome is likely to be achieved for around 33% of usual care participants compared to an anticipated 92% in the intervention group [23]. Unadjusted for the cluster design, this requires a total sample size of 20 patients. The intra-class correlation coefficient for this outcome will be much higher. Based on a value of 0.4, the study is still likely to have sufficient power to detect this difference.

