### Analysis

This is a single-blinded study with the statistician analyzing the results blinded to the study group of participants. The statistician analyzing the data will be based in a different geographical site from the team managing the study and collecting the data. The analyst will be provided with a data file from which all patient, practice, and study group identifying data has been expunged. These variables will be replaced in the analyst’s file with non-identifiable numeric codes. Before being provided with the data file for analysis, the principal investigator and one other investigator will check the data to ensure that all potentially identifying information has been removed.

The analysis will use a generalized linear mixed model to take account of both the dichotomous outcome variables and the cluster design. These models are more complex than generalized linear models or mixed linear models. The outcomes for individual patients will be the response variables, but we will take account of the cluster design and plan to fit practice and practice-treatment interaction effects as random effects. We may have to explore if the practice-treatment interaction effect has a non-zero value and fit a simpler model. PROC GLIMMIX in SAS will be used to fit the models [28-30].

Analysis of the outcomes will include all patients registered by the GPs, including those who eventually turn out to have a diagnosis other than TIA/stroke (*i.e.*, ‘intention-to-treat’ analysis). However, a pre-specified secondary analysis is of the main outcomes for only patients who were confirmed to have suffered an actual TIA or minor stroke by specialist assessment.

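### The 80% power for 90-day stroke is worked out for true TIA/minor stroke cases, but the main analysis takes all registered patients, for whom the plan's own low and middle yields give less than 80%

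*Protocol article*

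**What the plan says.** **Endpoint.** In the Protocol article, Outcome measures names "recurrent stroke within 90 days of initial presentation with TIA or stroke" as one of two primary outcomes. The secondary outcomes include "occurrence of recurrent TIA, myocardial infarction, major bleeding, and/or death within 90 days". The Sample size calculation opens in agreement: "The primary outcome is the proportion of participants who have recurrent stroke within 90 days of the presenting TIA/stroke". Its next sentence gives the planning rates as "10% of patients in the control group will have a stroke or TIA compared to 2% of patients in the intervention group". The Background reports, for one model of urgent care, an "80% reduction in 90-day stroke risk from 10.3% to 2.1" per cent, which is stroke alone.

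**Size.** The Sample size calculation gives 274 in total before clustering, for 80% power at 5% type I error. It plans 40 practices with an ICC of 0.01, and then states: "Based on an average of seven participants per practice, the adjusted sample size needed is 292". It calls this achievable with 2.5 full-time GPs per practice. It expects four to five registrations per GP over 12 months, "with an average of only two to three patients having actually suffered a true TIA or minor stroke", and says that a GP diagnostic accuracy of 50% to 80% has been allowed for.

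**Population.** The Analysis section states: "Analysis of the outcomes will include all patients registered by the GPs", including those who turn out to have another diagnosis. The analysis of specialist-confirmed cases is secondary. Practice engagement reports that 44 practices were recruited.

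**The concern.** The calculation and the main analysis appear to concern different patients. Seven per practice matches the expected true cases (2.5 × 2 to 3 = 5 to 7.5), not the expected registrations (2.5 × 4 to 5 = 10 to 12.5). The rates of 10% and 2% are those of patients who really had a TIA or minor stroke. Diagnostic accuracy enters the recruitment forecast but neither the rates nor the cluster size behind 292. The 80% therefore belongs to the secondary, confirmed-case analysis, and no power is given for the main one.

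The Discussion says that the trial was powered for the stroke outcome. A null stroke result would then be read against 80% power that the plan's middle assumptions do not support. The mixed endpoint label adds a second uncertainty, because a reader cannot tell which event the planning rates describe.

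**Working it through.** **1. The plan's figures.** Two-sided 5% (sidedness is not stated, but two-sided reproduces the result), 80% power, pooled variance, p1 = 0.10, p2 = 0.02, mean p = 0.06:

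n per arm = [1.96 √(2 × 0.06 × 0.94) + 0.8416 √(0.09 + 0.0196)]² / 0.08² = 137.15, so 274 in total.

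Design effect = 1 + (7 − 1) × 0.01 = 1.06. Then 137.15 × 1.06 = 145.4 per arm, rounded up to 146, so 292. Power at 292 is 80.2%. The arithmetic is sound.

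**2. Recruitment products.** At design effect 1.06 and undiluted rates, 40 × 7 = 280 gives 78.5% and 44 × 7 = 308 gives 82%. True cases expected from 40 practices are 40 × 2.5 × (2 to 3) = 200 to 300, midpoint 250. From 44 practices they are 220 to 330, midpoint 275.

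**3. The main analysis set.** Let r be registered and t true cases per GP, q = t/r, and b the 90-day stroke rate in registered patients without TIA/stroke. The document gives no value for b. I take 0 to 2%, equal in both arms, as an assumption.

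- Registered N = practices × 2.5 × r
- Stroke rates: 0.10q + b(1 − q) and 0.02q + b(1 − q)
- Design effect: 1 + (2.5r − 1) × 0.01, i.e. 1.09 to 1.115
- Power: the formula of step 1, with N/2 divided by the design effect as the arm size

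Worked midpoint with 40 practices: r = 4.5, t = 2.5, N = 450, q = 0.556. At b = 0 the rates are 5.56% and 1.11%. The design effect is 1.1025, so the effective arm size is 225/1.1025 = 204, and power is 71%.

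| Practices | r, t per GP | Registered / true | Power, b = 0 | Power, b = 2% | True cases alone |
|---|---|---|---|---|---|
| 40 | 5, 2 | 500 / 200 | 60% | 44% | 65% |
| 40 | 4, 2 | 400 / 200 | 61% | 50% | 65% |
| 40 | 4.5, 2.5 | 450 / 250 | 71% | 61% | 74% |
| 40 | 5, 3 | 500 / 300 | 78% | 70% | 81% |
| 40 | 4, 3 | 400 / 300 | 79% | 75% | 81% |
| 44 | 5, 2 | 550 / 220 | 64% | 48% | 69% |
| 44 | 4, 2 | 440 / 220 | 65% | 54% | 69% |
| 44 | 4.5, 2.5 | 495 / 275 | 75% | 65% | 78% |
| 44 | 5, 3 | 550 / 330 | 82% | 74% | 85% |
| 44 | 4, 3 | 440 / 330 | 83% | 79% | 85% |

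Crossing r = 4, 4.5, 5 with t = 2, 2.5, 3 at b = 0, none of the nine combinations reaches 80% with 40 practices. With 44, only the three at t = 3 do. At b = 2%, none of the 18 does.

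**4. Splitting the midpoint gap (40 practices).** Yield alone takes power from 80% to 74%. Including non-TIA patients takes it to 71% at b = 0, or to 61% at b = 2%. So most of the gap is yield if non-TIA patients are stroke-free, and dilution dominates if they are not.

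**5. Endpoint label.** With the Background's stroke-only 10.3% and 2.1% at N = 292 and design effect 1.06, power is 81%. Read as stroke-only rates, 10% and 2% lose nothing.

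**The case against.** **Best case for the plan.** Passing over the wording of one sentence, a reader can say that 292 lies inside the expected 200 to 300 true cases, that 44 practices at seven each exceed it, and that extra registrations largely offset dilution when non-TIA patients have almost no strokes. All of this is correct. It is why power does reach 80% near three true cases per GP with 44 practices, and why it would be wrong to say that the design cannot deliver 80% at all.

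**The 80% accuracy end.** Applying 80% accuracy to four to five registrations gives 82-92% power at b = 0. But it implies 0.8 × 4 to 5 = 3.2 to 4 true cases per GP, outside the stated two to three, so it does not remove the shortfall.

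**Stronger readings that the document does not support.** A reader might take 292 as registered patients, which gives 49% (q = 0.5) to 70% (q = 0.8) at b = 0. The text expects 400 to 500 registrations from 40 practices, so this reading does not fit. A reader might also infer from the label that the power was lost to a composite endpoint. No split between stroke and TIA is given, the preceding sentence names stroke alone, and the Background has nearly the same rates for stroke alone. Because the sample size section cites other references for its rates, the label cannot be fully settled, but no loss can be shown.

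**Approximation.** An exact calculation lifts both sides: about 84% for the plan's own case and 75% for the 40-practice midpoint. The gap remains.

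**The Discussion's caveat.** It warns that the stroke outcome may be hard to achieve and gives this as the reason for the second primary outcome. The ground given is outdated stroke rates, which covers neither dilution nor yield.

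**Conclusion.** The point stands in a limited form. The sums are right, but the stated 80% applies to true cases analysed alone, while the main analysis includes everyone registered. The departure from 80% is material at low and middle yields, modest at the best yields with 40 practices, and absent at the best yields with 44 if non-TIA patients are stroke-free.

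This rests on the plan's own yields, ICC and rates, on the assumed range for b, and on the inference that seven per practice means true cases. The document does not say so, but its registration figures cannot produce seven. The mismatch between 40 × 7 = 280 and 292 is minor (78.5% against 80%). The endpoint label is an ambiguity to clear up, not a proven loss.

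**What to change.** In the sample size section:

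- State that 10% and 2% are stroke-only rates in true TIA/minor stroke cases and remove the reference to TIA, or give the stroke-only rates that were meant.
- Say that 292 refers to true cases.
- Restate power for the all-registered analysis using diluted rates, 10 to 12.5 registered per practice and 44 practices. Show the assumed stroke rate in non-TIA patients as a range: at the midpoint, about 75% at 0 and 65% at 2%.
- Give the confirmed-case power separately (about 78% at 275 true cases).
- Reconcile 40 × 7 = 280 with 292, and note that 44 × 7 = 308 gives 82%.

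This costs a few sentences and a less favourable stated power. It needs no further recruitment and no change to the main analysis. Promoting the confirmed-case analysis instead would be a larger step: confirmation comes after randomisation, so it would need a safeguard against bias.

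### The 80% power and the 10% v 2% difference for 90-day stroke are calculated for confirmed TIA/minor stroke patients, but the main analysis is of all registered patients

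*Protocol article*

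**What the plan says.** All references are to the protocol article.

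- **Sample size calculation, outcome and rates.** "The primary outcome is the proportion of participants who have recurrent stroke within 90 days of the presenting TIA/stroke". The effect assumed is: "we estimate that 10% of patients in the control group will have a stroke or TIA compared to 2% of patients in the intervention group". I take these as stroke rates, because stroke is the outcome being sized.
- **Sample size calculation, size.** The unadjusted requirement is "a total sample size of 274, one-half in each of two treatment arms", for 80% power at a 5% type I error rate. For clustering: "We planned to recruit 40 practices, representing clusters, and used an intra-class correlation coefficient of 0.01". With seven participants per practice this becomes 292.
- **Sample size calculation, feasibility.** The 292 is justified by 2.5 GP full-time equivalents per practice and two to three TIA/minor stroke patients per GP per year. The section adds: "The sample size calculation also takes into account an expected 50% to 80% [13] GP diagnostic accuracy". It expects that "an average of four to five patients will be registered in the study per GP over 12 months", of whom only two to three will be true cases.
- **Analysis.** "Analysis of the outcomes will include all patients registered by the GPs, including those who eventually turn out to have a diagnosis other than TIA/stroke". The analysis restricted to specialist-confirmed TIA or minor stroke is labelled a pre-specified secondary analysis.
- **Practice engagement.** 44 practices were recruited, against 40 planned.

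**The concern.** The section says that diagnostic accuracy has been allowed for. For the population in the main analysis it has not. Seven per practice agrees with 2.5 × 2 to 3 = 5 to 7.5 true cases per practice. It does not agree with 2.5 × 4 to 5 = 10 to 12.5 registered patients. The 10% and 2% are not diluted for patients who turn out to have something else, and the design effect uses the smaller cluster.

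The 80% power and the 8-point difference are thus given for an analysis that the plan calls secondary. Two misreadings could follow. A null result in the main analysis could be judged against a power that was never calculated for it. A tool that works exactly as assumed would show a difference of about 4 to 6 points in the main set and could be taken for a weaker effect than planned.

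**Working it through.** **Inputs from the plan.** Rates 10% and 2%; two-sided 5% (sidedness is not stated, but two-sided reproduces the figure); 80% power; intra-class correlation 0.01; seven per practice; accuracy 50% to 80%; 2.5 GPs per practice; 4 to 5 registered and 2 to 3 true cases per GP; 44 practices.

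**Assumptions, not in the plan.** The confirmed share f is the same in both arms. Patients without TIA/stroke have a 90-day stroke rate r that is equal in both arms, taken over 0 to 2%.

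**1. The plan's own figure.** Pooled two-proportion formula, no continuity correction, with p̄ = 0.06:

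n per arm = [1.96 √(2 p̄(1−p̄)) + 0.842 √(p₁(1−p₁) + p₂(1−p₂))]² / (p₁−p₂)² = 137.2, which gives 274 in total.

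Design effect = 1 + (7−1) × 0.01 = 1.06. Then 137.2 × 1.06 = 145.4, or 146 per arm and 292 in total. Power at 292/1.06/2 = 137.7 effective patients per arm is 80.2%. So 274 and 292 follow from undiluted rates and the true-case cluster size.

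**2. The all-registered set when 292 true cases are reached.** Registered N = 292/f; cluster size m = 7/f; design effect = 1 + (m−1) × 0.01; rate in each arm = f·p + (1−f)·r. The expected difference is f × 8 points whatever r is.

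| f | N | m | Design effect | Rates at r = 0 | Difference | Power r = 0 | r = 1% | r = 2% |
|---|---|---|---|---|---|---|---|---|
| 0.80 | 365 | 8.75 | 1.078 | 8.0% v 1.6% | 6.4 | 78.9% | 77.4% | 75.8% |
| 0.65 | 449 | 10.8 | 1.098 | 6.5% v 1.3% | 5.2 | 77.8% | 74.3% | 71.1% |
| 0.50 | 584 | 14.0 | 1.130 | 5.0% v 1.0% | 4.0 | 76.1% | 69.7% | 64.1% |

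Using 292/40 = 7.3 true cases per practice instead of seven moves the design effect to 1.081 to 1.136 and power by about 0.2 points.

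Against 80.2%, the loss at r = 0 is 80.2 − 78.9 = 1.3 to 80.2 − 76.1 = 4.1 points.

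**3. Exact check.** Exact power of the uncorrected chi-square test at the same effective sizes, r = 0: 82.8%, 82.1% and 80.7% for f = 0.80, 0.65 and 0.50. The undiluted design gives about 84% on this scale. At r = 1% the values are 80.9%, 77.8% and 72.8%.

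**4. The plan's forecast with the 44 practices recruited, at the midpoint.** Registered: 44 × 2.5 × 4.5 = 495. True cases: 44 × 2.5 × 2.5 = 275. f = 275/495 = 0.556; m = 11.25; design effect 1.1025; rates 5.56% v 1.11% at r = 0.

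- All registered: 495/1.1025/2 = 224.5 effective per arm, power 74.8% (69.6% at r = 1%).
- Confirmed only: m = 6.25, design effect 1.0525, 275/1.0525/2 = 130.6 effective per arm, power 78.0%.
- The gap due to the population is 78.0 − 74.8 = 3.2 points. The rest of the distance from 80.2% arises because 275 is below 292.
- At the low and high ends of the forecast, all-registered power at r = 0 is 65.5% and 81.8%, against 69.0% and 84.6% for confirmed cases.

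**The case against.** **The loss may be negligible.** Misdiagnosed patients come on top of the true cases, so if they have no strokes the expected number of strokes is unchanged. What remains is a small loss from dilution and the larger design effect. This stands: it is why the figure is 76% to 79% and not far lower, and why the exact calculation stays above 80%. A reader might infer that the trial simply lacks its stated power, but the plan's own inputs do not establish that. A loss beyond a few points needs a non-zero stroke rate in non-cases. Such a rate is plausible, but the plan does not give one.

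**Lower figures are easy to produce but are not due to this defect.** A reader might take 292 as the total to be registered and compute 49% to 70% (f = 0.5 to 0.8, design effect 1.06). The text argues against that: registration runs for a fixed 12 months, and 40 practices are expected to register 400 to 500 patients. A reader might also quote 71% from the midpoint forecast in 40 practices (450 registered, 250 true). Most of that shortfall is accrual, since confirmed-only power is already 74% with 250 true cases, and the figure ignores the 44 practices recruited.

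**The 10% v 2% could have been meant for all registered patients.** The true-case rates would then have to be 10/0.8 = 12.5% to 10/0.5 = 20% in the control arm. The Background cites 10.3% falling to 2.1%, and the feasibility argument counts true cases, so this reading does not fit.

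**The plan softens the harm elsewhere.** The confirmed-case analysis is pre-specified and would sit beside the diluted result. The Discussion admits that the stroke outcome may be hard to achieve and gives this as the reason for a second primary outcome. Both points stand, but neither supplies a power for the main analysis, and the Discussion still says that the study was powered for stroke.

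**Conclusion.** The point holds as a mismatch between the population that was sized and the population in the main analysis. It is not an arithmetic error, as 274 and 292 both reproduce. The stated 80% power, the 8-point difference and the design effect of 1.06 describe the confirmed-case secondary analysis, and the claim that diagnostic accuracy was allowed for is true only of the registration count.

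Given 292 true cases, power in the main analysis is about 76% to 79% with no strokes in non-cases and about 70% to 77% at an assumed 1%, by the plan's own type of formula. The expected difference of 4.0 to 6.4 points is the firmer result: it needs only the plan's 50% to 80% accuracy, the same confirmed share in both arms, and equal stroke rates in non-cases. How far power falls depends mainly on stroke risk in the misdiagnosed, which the plan does not state.

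**What to change.** Revise one paragraph of the Sample size calculation:

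- State that 10% v 2%, seven per practice, the design effect of 1.06 and the total of 292 refer to confirmed TIA/minor stroke patients, and that 292 is not a count of registrations.
- Give the power for the all-registered analysis, using diluted rates (5% to 8% v 1% to 1.6% if non-cases have no strokes, with a range for a non-zero rate), about 11 registered patients per practice, and a design effect of about 1.08 to 1.14 over the accuracy range.
- Base the forecast on the 44 practices recruited: about 75% at 495 registered and 275 true cases, noting that only about 3 points of the shortfall come from the choice of population.
- State the expected difference in the main set, 4.0 to 6.4 points, so that the result is read against the right target.

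The cost is text and a slightly less favourable power statement. No extra patients and no change to the design or the analysis populations are needed.
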